## Discussion

With the rapid advancement of neonatal intensive care technology, NICU are facing increasing challenges. Improving the prognosis of small gestational age premature infants, aiming to achieve higher survival rates, reducing complications, and enhancing future quality of life-has become a central focus in the treatment of these infants. To address these challenges, NICU must adopt new concepts, adjust treatment policies, and implement innovative clinical procedures. DCC and MISA are prime examples of such advancements.

DCC has been utilized for term infants for many years, demonstrating positive effects on hematocrit levels and iron reserves. It is now a standard recommendation for term infants following delivery; however, its benefits for premature infants, particularly those who are extremely premature, remain unclear. Recently, an increasing number of studies have investigated DCC in premature infants, with multiple systematic reviews and meta-analyses highlighting the potential for improved outcomes through various umbilical cord management strategies (7, 16). Despite these findings, a unified global recommendation has yet to be established. A meta-analysis published in The Lancet in 2023 reaffirmed that DCC positively impacts reducing in-hospital mortality in premature infants (17). Our NICU, which has focused on treating premature infants gently for many years, began gradually implementing DCC for those without contraindications in 2023. We have developed operating procedures for the delivery and operating rooms and provided training for obstetricians and neonatologists to ensure the stable and safe application of DCC. However, due to the recent implementation, no relevant research has been conducted yet.

MISA, which involves the insertion of a thin tube into the airway to deliver pulmonary surfactant alongside non-invasive respiratory support, reduces the need for mechanical ventilation and decreases the incidence of BPD. This approach is already a common recommendation in clinical guidelines (18). As one of the early adopters of MISA in China, our hospital has previously documented its effectiveness in improving BPD outcomes and has accumulated extensive experience with MISA procedures.

DCC not only enhances the transfer of blood from the placenta to the fetus, improving hemoglobin reserves in premature infants, but it also stabilizes the establishment of pulmonary circulation in the early postnatal period. Since placental circulation provides 30%–50% of cardiac blood flow, immediate clamping of the umbilical cord can lead to a significant drop in venous return and cardiac output. DCC facilitates a smoother transition until premature infants can establish effective pulmonary ventilation and circulation. Thus, DCC serves as a crucial component of early respiratory and circulatory management for these infants. This study aims to determine whether the simultaneous application of DCC and MISA further enhances survival and prognosis in premature infants. Given our recent implementation of DCC for infants born before 30 weeks, we designed a NICU quality improvement study to evaluate the efficacy of DCC combined with MISA by comparing prospective and retrospective cohorts.

Despite the potential of this study, there are some limitations to consider. As a quality improvement study, data for the ICC and MISA and ICC and tracheal intubation groups were collected retrospectively, which may introduce biases due to variations in hospitalization years and treatment approaches. Furthermore, the retrospectively collected data are based on the diagnosis, treatment, and evaluation conducted by clinicians, and there may be variations in this process. To minimize these discrepancies, we limited the study to preterm infants from the past six years for the retrospective cohort. Additionally, both the prospective and retrospective cohorts adhered to the same inclusion and exclusion criteria to reduce intergroup differences and enhance the validity of the conclusions.

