**Methods and design:**

This is a single-center quality improvement study evaluating three treatment regimens for neonates with NRDS born at a gestational age of <30 weeks: (1) Retrospective data collection of cases treated with the conventional approach of ICC + tracheal intubation between 2017 and 2020 (*n* = 222); (2) Retrospective data collection of cases treated with ICC + MISA between 2021 and 2025 (*n* = 222); (3) Planned collection of medical records of cases treated with DCC + MISA between 2025 and 2027 (*n* = 74).The study aims to assess the incidence of BPD and survival outcomes associated with each regimen. Meanwhile, it will compare the short-term efficacy, safety, and long-term outcomes of these three treatment strategies, thereby providing valuable evidence for clinical treatment decision-making.

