**Discussion:**

Current research indicates that both DCC and MISA positively impact the prognosis of very premature infants and help reduce the incidence of BPD. However, there is limited research on whether the combined use of DCC and MISA can further improve survival rates and reduce the incidence of BPD in this vulnerable population. Our NICU has gradually implemented MISA in respiratory management since 2021 and adopted cord management with DCC since 2025. This study retrospectively analyzes data from previous groups: those receiving ICC with MISA, and those receiving ICC with tracheal intubation. We will compare this with prospective data from the DCC combined with MISA group to assess differences in BPD occurrence, other complications and overall outcomes. This study will also collect and analyze the annual application rates and operational success rates of MISA and DCC, so as to promote quality improvement in the NICU. Through this study, we aim to determine whether the combination of DCC and MISA offers greater benefits in improving the prognosis of very premature infants, ultimately providing a stronger foundation for early respiratory and circulatory management strategies for infants born before 30 weeks.

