However, there are limited reports in China regarding the implementation of DCC in premature infants born at less than 30 weeks gestation. Our hospital began adopting DCC for preterm infants in 2025 and has developed and standardized the operational procedures for this practice. However, relevant clinical studies have yet to be conducted. NRDS is a condition resulting from a deficiency of pulmonary surfactant in the alveoli. It is the most common respiratory issue encountered by very premature infants, who often experience progressively worsening respiratory distress shortly after birth. Treatment for NRDS involves respiratory support and the administration of exogenous PS. Traditionally, this is done through tracheal intubation. However, recent clinical studies have demonstrated that MISA offers several advantages over tracheal intubation (8). MISA effectively reduces the need for invasive mechanical ventilation within the first 72 h and plays a significant role in lowering the incidence of BPD (9).

With advancements in DCC and MISA technology in NICU settings, these approaches have become the preferred options for very premature infants who are breathing spontaneously at birth. To further assess the safety and effectiveness of DCC combined with MISA in our hospital's NICU for premature infants born at less than 30 weeks gestation, we propose this quality improvement study. The study aims to compare the incidence and prognosis of BPD and other complications before and after the implementation of DCC and MISA in the NICU.

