Our hospital comprehensively implement the MISA since 2021 and has gained extensive clinical experience in treating NRDS in premature infants using this method. We previously conducted a prospective multicenter study comparing MISA with tracheal intubation for surfactant administration shortly after birth. The results indicated that the incidence of BPD and hemodynamically significant patent ductus arteriosus (hsPDA) was lower in the MISA group, highlighting its suitability for premature infants born at less than 30 weeks gestation (10, 11). Our hospital has gradually implemented DCC for premature infants prior to this research and has established a comprehensive protocol for its application in the delivery room and during surgical procedures. As a result, our NICU is well-equipped to perform DCC combined with MISA for infants born at less than 30 weeks gestation. Based on previous research findings, this study specifically targets premature infants under 30 weeks, a group that exhibits a relatively high incidence of BPD. By monitoring the respiratory and overall health outcomes of these infants following the application of DCC combined with MISA, we aim to evaluate the effectiveness of this NICU quality improvement measure in enhancing the prognosis of very premature infants.

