## Methods

### Study design

For preterm infants with a gestational age of <30 weeks diagnosed with NRDS, along with the continuous advancement of diagnosis and treatment in the NICU, they were divided into 3 phases based on time and treatment methods:
From 2017 to 2020, retrospective data were collected from infants treated with ICC combined with tracheal intubation for pulmonary surfactant administration;In 2021, after the promotion of MISA in the NICU, retrospective data were collected from 2021 to 2025 of infants treated with ICC combined with MISA;Starting from 2025, as the NICU has popularized the operational procedures for DCC in preterm infants, a prospective cohort study is planned to be conducted, and data will be collected from infants treated with DCC combined with MISA.This study evaluated the incidence of BPD, survival status, and other comorbidities associated with each treatment regimen, so as to provide references for the formulation of clinical decisions regarding treatment option selection. The operational process of this study is illustrated in Figure 1.

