#### ICC+MISA group

From Jan.1, 2021 to Dec. 31, 2024.Umbilical cord clamping is performed within 20 s after birth. Infants are diagnosed with NRDS and receive a therapeutic dose of PS via MISA within the first 2 h after birth.

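### The start of DCC is dated both 2025 and 2023; if 2023 holds for infants under 30 weeks, late ICC+MISA controls are selected in a way that favours DCC+MISA

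*Protocol article*

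**What the plan says.** All statements are in the protocol article.

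**Start of DCC**
- Abstract, Discussion paragraph: the unit "adopted cord management with DCC since 2025".
- Background: "Our hospital began adopting DCC for preterm infants in 2025".
- Study design: the third phase is introduced with "Starting from 2025, as the NICU has popularized the operational procedures for DCC in preterm infants".
- Background, further on and undated: "Our hospital has gradually implemented DCC for premature infants prior to this research".
- Discussion: the unit "began gradually implementing DCC for those without contraindications in 2023". Later the same section calls the use of DCC under 30 weeks recent, again without a date.

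**Groups**
- Research grouping assigns infants by time phase and by the treatment they received.
- ICC+MISA group: "From Jan.1, 2021 to Dec. 31, 2024.Umbilical cord clamping is performed within 20 s after birth". The Abstract describes the same group as "Retrospective data collection of cases treated with ICC + MISA between 2021 and 2025".
- DCC+MISA group: 31 August 2025 to 31 October 2027. It takes infants whom prenatal evaluation found free of DCC contraindications and in whom a 60 s delay succeeded.
- The exclusion criteria shared by all groups do not mention contraindications to DCC.

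**The concern.** The study is not randomised. Its main contrast, and the only one used to size it, is DCC+MISA against ICC+MISA. That contrast is cleanest if the control window is a period in which immediate clamping was the routine for everyone. A 2025 start supports this; a 2023 start does not.

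If DCC was offered from 2023 to infants under 30 weeks without contraindications, those infants fail the 20 s criterion and drop out of the control group. The infants still clamped immediately in 2023 and 2024 would then more often have a contraindication. The comparison arm admits only infants without one. Better-risk infants would thus be missing from the later control years, control BPD would rise, and part of the observed difference would reflect who was left in the control group.

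**Working it through.** **1. The dates side by side.** The Background says DCC for preterm infants began in 2025; the Discussion says it began in 2023. Both cannot be the start. A reconciling reading is gradual use from 2023 and routine use from 2025. It removes the contradiction but still places DCC inside the control window.

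**2. Overlap with the control window.** From 1 January 2021 to 31 December 2024 is 1461 days. The Discussion gives a year but no month.

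| Assumed start | Days left in window | Share of window |
|---|---|---|
| 1 Jan 2023 | 731 | 50% |
| 1 Jul 2023 | 550 | 38% |
| 31 Dec 2023 | 367 | 25% |

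These are shares of calendar time, not of infants.

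**3. The plan's sample size, reproduced.** Inputs from Sample size calculation: p1 = 0.29, p2 = 0.14, k = 3, z-values 1.96 and 0.84.
- n2 = (2.80)² × (0.29×0.71/3 + 0.14×0.86) / 0.15² = 7.84 × (0.0686 + 0.1204) / 0.0225 = 65.9, rounded up to 66; n1 = 3 × 66 = 198.
- With 10% loss: 66/0.9 = 73.3, rounded up to 74; 3 × 74 = 222.
- Power at 66/198: SE = √(0.2059/198 + 0.1204/66) = 0.0535; Φ(0.15/0.0535 − 1.96) = 0.80.

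The stated figures are correct. The date conflict does not touch this arithmetic; it bears on who the controls are.

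**4. Selection, for illustration.** Assumptions that are not in the document: DCC began on 1 January 2023; eligible births are even over the window; half of the eligible 2023–2024 infants received DCC; all eligible infants average 29% BPD under ICC; the remaining 2023–2024 controls have BPD rate r. The years 2021–2022 then carry weight 1 and 2023–2024 weight 0.5:

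control BPD = (0.29 + 0.5r) / 1.5

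| r | Control BPD | Excess over 29% | Implied ICC risk of removed half (2×29% − r) |
|---|---|---|---|
| 35% | 0.465/1.5 = 31.0% | 2.0 points | 23% |
| 40% | 0.490/1.5 = 32.7% | 3.7 points | 18% |

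**5. Power if only controls born before 2023 are kept, for illustration.** Assuming a pool of 222 (198 evaluable) spread evenly over the window, 99 evaluable controls remain.
- SE = √(0.2059/99 + 0.1204/66) = 0.0625; power = Φ(0.15/0.0625 − 1.96) = 0.67.

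**The case against.** **The 2023 start may not concern this population.** The sentence in the Discussion speaks of premature infants in general, and a later one calls DCC under 30 weeks recent. If the 2023 start covered only more mature infants, the control window is sound. This stands as a real possibility, but the text does not say so.

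**The plan already limits the problem.** All groups require spontaneous breathing and exclude intubation before surfactant, haemorrhagic shock, air leak and early-onset sepsis. Mode of delivery, maternal complications, Apgar score and cord gases are collected and may enter the adjusted model. Quality improvement-related indicators include the yearly DCC rate among all admissions of 23 to 29+6 weeks, which should show the uptake if it covers the retrospective years. The Discussion also concedes possible bias from differing years and treatment approaches. All this tempers the selection. It does not remove it: DCC contraindication is not among the listed baseline variables, and the adjusted model takes in only variables with P < 0.1.

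**Stronger readings that the document does not support**
- A reader might infer that DCC-treated infants sit among the controls and dilute the effect. Grouping is by treatment received, and "Umbilical cord clamping is performed within 20 s after birth" is part of the control definition, so a correctly classified control did not have DCC. Contamination would need missing or misrecorded clamping times.
- A reader might infer that half the controls are affected. Half is the upper end of the range, for calendar time, and the rollout was gradual.
- A reader might set residual BPD at 50%, which gives control BPD of (0.29 + 0.25)/1.5 = 36% and a 7-point excess. That implies 2×29 − 50 = 8% BPD under ICC in the removed infants, below the 14% the plan hopes to reach with DCC.
- A reader might take the 31 August 2025 start of the prospective cohort, which leaves out any earlier DCC+MISA infants, as an error. It is a legitimate design choice.

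**Conclusion.** The conflict between 2025 and 2023 is certain, stands in current text and is not resolved anywhere in the article. Its consequence is conditional. If the 2023 start applied to infants under 30 weeks, 25% to 50% of the ICC+MISA window overlaps the rollout. The later controls would then be enriched for infants with DCC contraindications, against an arm that requires none. The direction favours DCC+MISA.

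The document gives no DCC uptake for 2023–2024, so the size cannot be computed. Under the assumptions in step 4 it is about 2 to 4 points of the planned 15. The point is more than clerical because the date determines whether the control years are an era of routine immediate clamping.

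**What to change.** 1. Reconcile the Abstract, Background, Study design and Discussion, and state one date on which DCC began for infants under 30 weeks. The yearly DCC rates already planned can supply it.
2. If that date falls before 31 December 2024, limit ICC+MISA controls to infants with no documented DCC contraindication, matching the DCC+MISA group. Add a sensitivity analysis using only controls born before the date. Repeating the 20 s limit adds nothing, since it already defines the group.
3. State the resulting number of controls and the power. The 67% in step 5 is only a guide, because the article does not give the size of the eligible pool.
4. Optional, and dependent on the reconciled date: describe any DCC+MISA infants born before 31 August 2025 in a supplementary analysis.

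The cost is a text correction and some chart review for contraindications. If 2023 proves right, there will also be fewer controls and a lower stated power. The corrections in items 1 to 3 require no additional prospective recruitment.

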## Conclusion

If the combination of DCC and MISA proves effective in reducing BPD in premature infants born before 30 weeks and enhances their prognosis compared to the ICC and MISA or ICC and tracheal intubation groups, this finding will provide a theoretical foundation for improving the quality of care in the NICU and optimizing early respiratory and circulatory management for small gestational age premature infants.
